### Step four: assess workflow modification effect on pMTCT cascade

Using routinely reported pMTCT cascade data from the pMTCT step that was selected for improvement, facility staff will monitor improvements in relevant indicators for two to six weeks following the introduction of the facility-specific workflow adaptation. Monitoring data will be analyzed visually and using descriptive statistics after a short time period, relying on improvements in the absolute increase in the proportion of women or infants successfully progressing through the step of interest to capture large, rapid improvements associated with the introduction of the adaptation.

### Step five: repeat analysis and improvement cycles

Systems engineering process improvements are by definition iterative, entailing ongoing testing of innovations that respond to contextually specific, modifiable barriers. Facility staff will repeat steps one through five at the end of each change cycle, focusing on identifying new approaches to modify previously identified barriers, or if the first cycle was successful, focusing on improving priority bottlenecks identified in a repeated systems analysis.

### Adaptation of the analysis tool and improvement intervention

To ensure intervention adequacy and the implementation process, the SAIA intervention was piloted in five facilities for six months in Sofala, Mozambique. Through the piloting phase, the PCAT was adapted and translated from Portuguese into French and English, a toolkit was developed to support introduction of the intervention, and standard operating procedures were written to guide the implementation process and data collection procedures for the trial.

### Process for introducing the SAIA intervention

The SAIA intervention is designed to be introduced to each study facility over a four-day period (Table 2). On day one, trained study nurses hold a meeting with representatives from sectors of the health facility relevant to pMTCT, which may include ANC, maternity, postpartum care, at-risk child care, laboratory, and pharmacy staff. The specific composition depends on the individual health facility structure. At this initial meeting the study objectives and core components of the intervention are introduced, a calendar of activities for the week and across the six-month intervention period are developed, and PCAT results populated with the facility’s data from the most recent six months shared. On days two and three, study nurses work with facility staff to develop process maps for relevant services (ANC, maternity, postpartum care, and at-risk child care) with up to two health workers from each sector (including the sector in-charge and a second staff member who is knowledgeable about the health facility and are willing to participate in the exercise). A feedback meeting is held at the end of day three to have staff from each sector share their process maps, prioritize which sector to target with the initial improvement cycle, and brainstorm potential solutions. On day four, study nurses work with facility staff to prioritize solutions, and develop an implementation plan that explicitly records: the change(s) to be tested; the individual(s) responsible for each change; metrics to assess service improvement; a future process map to reflect the innovation; and a follow-up visit schedule. Subsequent follow-up visits are planned weekly for the first four weeks, bi-weekly for the next eight weeks, and subsequently according to the schedule agreed upon by facility staff and based on support needs.

**Table 2 T2:** SAIA introduction schedule

**Activity**	**Day 1**	**Day 1**	**Day 2**	**Day 2**	**Day 3**	**Day 4**
	**AM**	**PM**	**AM**	**PM**		
Intro to SAIA and PCAT	X					
Process mapping						
ANC		X				
Maternity			X			
Postpartum/At-risk care				X		
Feedback session					X	
Implementation start						X

ANC: Antenatal care; HIV: Human immunodeficiency virus; PCAT: PMTCT cascade analysis tool; SAIA: Systems Analysis and Improvement Approach.

It is expected that each change cycle will require four to six weeks of testing to allow for sufficient time to detect desired effects on the pMTCT cascade, but to be short enough to allow for multiple iterations during the six-month intervention period. After each cycle, study staff will work with facility staff to review the original implementation plan, describe what actually occurred (including review of planned metrics to assess improvements), discuss what worked well and why, and identify what could be improved and how. The five-step SAIA intervention cycle will again be repeated to review PCAT data, update process maps, and develop the next change cycle. It is expected that between four and six change cycles will be implemented in each facility over the six-month intervention period.

### Study timeline

The total data collection and implementation period is designed to cover 21 months, which includes 12 months of pre-intervention data collection, six months of intervention implementation, and three months of post-intervention data collection. The 12-month timeframe for pre-intervention data collection was chosen to generate stable baseline study outcomes despite monthly temporal fluctuations in these measures. A total of six months was selected for implementing the study intervention to provide sufficient time for the intervention to be adopted and lead to improvements, to allow for a sufficient number of iterative system analysis and improvement cycles to lead to sustainable performance improvements (assuming that each cycle will last on average four to six weeks, this timeframe will allow for between four and six cycles per facility), and to be feasible to complete within the specified funding timeline.

### Study measures

#### Primary study outcomes

The three study outcomes include the proportion of women screened for HIV during their first ANC visit; the proportion of HIV infected women receiving antiretroviral medications during pregnancy (either bi-prophylaxis using AZT or combination antiretroviral therapy); and the proportion of infants born to HIV-infected women screened for HIV at six weeks postpartum (or two months in the case of Côte d’Ivoire, following national norms) (Table 3). These outcome measures were selected because they reflect successful progression through steps in the pMTCT cascade, they are likely sensitive to system-level improvements, and they represent steps that, if changed, would meaningfully alter patterns of HIV transmission or access to maternal and infant HIV care. Furthermore, these measures reflect national pMTCT protocols, and are therefore well understood and available in all three study countries. Data will be collected over 12 months before the intervention, during the six-month intervention, and three months after the intervention in both intervention and comparison facilities (21 time points and 36 measurements per time point).

**Table 3 T3:** pMTCT outcome measures

**Study measure**	**Numerator/Denominator**
1. Uptake of HIV counseling and testing	$\frac{\#\mathrm{women}\;\mathrm{counseled}\;\mathrm{and}\;\mathrm{tested}\;\mathrm{for}\;\mathrm{HIV}\;\mathrm{in}\;\mathrm{their}\;\mathrm{first}\;\mathrm{ANC}\;\mathrm{visit}}{\#\mathrm{first}\;\mathrm{ANC}\;\mathrm{visits}}$
2. Use of appropriate ARVs in pregnancy for prophylaxis or initiation of cART	$\frac{\#\mathrm{HIV}‒\mathrm{infected}\;\mathrm{pregnant}\;\mathrm{women}\;\mathrm{starting}\;\mathrm{AZT}\;\mathrm{prophylaxis}\;\mathrm{or}\;\mathrm{cART}}{\#\mathrm{women}\;\mathrm{testing}\;\mathrm{HIV}‒\mathrm{positive}\;\mathrm{in}\;\mathrm{ANC}\;3\;\mathrm{months}\;\mathrm{previously}}$
3. Infant HIV determination	$\frac{\#\mathrm{infants}<6\;\mathrm{weeks}\;\mathrm{of}\;\mathrm{age}\;\mathrm{receiving}\;a\;\mathrm{PCR}\;\mathrm{test}}{\#\mathrm{women}\;\mathrm{testing}\;\mathrm{HIV}‒\mathrm{positive}\;\mathrm{in}\;\mathrm{ANC}\;5\;\mathrm{months}\;\mathrm{previously}}$

ANC: Antenatal care; ARV: Antiretroviral; AZT: Azidothymidine; cART: combination antiretroviral therapy; HIV: Human immunodeficiency virus; PCR: Polymerase chain reaction.

All primary outcome measures are calculated as a monthly average (continuous percentage between 0% and 100%). Notably, outcome measures for study measures on use of appropriate ARVs in pregnancy for prophylaxis or initiation of cART, and infant HIV determination, include numerators and denominators from different time periods due to time progression between service contacts that can be represented by available data. For the use of appropriate ARVs in pregnancy, the delay between the service contact in the numerator (the number of pregnant women receiving AZT or cART) and denominator (number of women testing HIV positive in ANC) is estimated to be two months. This two-month delay reflects a mean gestational age of first ANC visit of 25 weeks, or approximately three months before initiation of AZT or cART. The recommended timeframe for PCR testing of infants is on average five months after the first ANC visit, where the majority of pregnant women undergo HIV testing.

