**Methods:**

This study employs a two-arm, longitudinal cluster randomized trial design. The unit of randomization is the health facility. A total of 90 facilities were identified in Côte d’Ivoire, Kenya and Mozambique (30 per country). A subset was randomly selected and assigned to intervention and comparison arms, stratified by country and service volume, resulting in 18 intervention and 18 comparison facilities across all three countries, with six intervention and six comparison facilities per country. The SAIA intervention will be implemented for six months in the 18 intervention facilities. Primary trial outcomes are designed to assess improvements in the pMTCT service cascade, and include the percentage of pregnant women being tested for HIV at the first antenatal care visit, the percentage of HIV-infected pregnant women receiving adequate prophylaxis or combination antiretroviral therapy in pregnancy, and the percentage of newborns exposed to HIV in pregnancy receiving an HIV diagnosis eight weeks postpartum. The Consolidated Framework for Implementation Research (CFIR) will guide collection and analysis of qualitative data on implementation process.

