Increase the proportion of eligible HIV-infected pregnant women who initiate cART during pregnancy	Initiate cART for eligible pregnant women after the first counseling visit post determination of eligibility rather than requiring completion of three counseling visits before initiating cART (while maintaining subsequent counseling visits post-cART initiation).
Increase the proportion of HIV-exposed infants receiving HIV screening with PCR at six weeks of age	Attach ANC cards with HIV exposure data to the well child monitoring card at birth for institutional deliveries in order to systematically identify exposed infants at the six week well-child care visit.

ANC: antenatal care; cART: Combination anti-retroviral therapy; CD4: Cluster of differentiation 4; HIV: Human immunodeficiency virus; PCR: Polymerase chain reaction.

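### The infant-testing primary outcome has three inconsistent definitions, and Table 3's age limit, if applied literally, leaves out tests done on the schedule that the text describes

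*Protocol article*

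**What the plan says.** Three places in the protocol article define this outcome.

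- **Study measures, Primary study outcomes (text).** The outcome is the proportion of "infants born to HIV-infected women screened for HIV at six weeks postpartum (or two months in the case of" Côte d'Ivoire). The text attributes this exception to national norms and says that the outcome measures in general reflect national protocols.
- **Table 3, row 3.** The numerator is the number of infants under six weeks of age who receive a PCR test. In the typesetting code of the formula the limit reads "infants}<6\;\mathrm{weeks}\;\mathrm{of}\;\mathrm{age". The row makes no exception for any country. The denominator is women testing HIV-positive in antenatal care five months previously.
- **Abstract, Methods.** The outcome is "the percentage of newborns exposed to HIV in pregnancy receiving an HIV diagnosis eight weeks postpartum", again without distinction by country.

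Two other places bear on the timing. Table 1 gives an illustrative workflow change meant to raise the proportion of "HIV-exposed infants receiving HIV screening with PCR at six weeks of age", using the antenatal card to "systematically identify exposed infants at the six week well-child care visit". The paragraph after Table 3 explains the denominator lag: "The recommended timeframe for PCR testing of infants is on average five months after the first ANC visit". It also gives a mean gestational age of 25 weeks at that first visit.

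**The concern.** Table 3 is the only place where the article sets out a numerator and a denominator, so a reader would take it as the counting rule. Its strict limit of under six weeks does not fit the sentence that cites it. A test done at six weeks falls outside the limit, and so does a test at two months. The illustrative change in Table 1 aims to increase tests at the six-week visit, and the printed numerator would not credit them.

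The event also differs. Table 3 counts a test, the text counts screening, and the abstract counts a diagnosis.

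This is one of three primary outcomes, and the Analysis section plans sub-analyses by country. Country teams that read the definition differently would produce outcomes that cannot be compared or pooled cleanly. The double extraction described under Data sources would not reveal the problem, because two extractors who apply the same limit will agree. Several definitions left standing also allow a choice among them after the data are seen.

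**Working it through.** **1. The definitions side by side**

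| Place | Event counted | Age | Country exception |
|---|---|---|---|
| Table 3, row 3 | PCR test | under 6 weeks | none |
| Text citing Table 3 | screened for HIV | at 6 weeks | two months in Côte d'Ivoire |
| Abstract | HIV diagnosis | 8 weeks | none |
| Table 1 (illustration) | PCR screening | at 6 weeks | none |

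A test at exactly six weeks fails the Table 3 limit. Two months is 2 × 4.348 = 8.7 weeks (365.25 / 12 / 7 = 4.348 weeks per month), so a two-month test misses the limit by 8.7 − 6 = 2.7 weeks.

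**2. The plan's own five-month lag**

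Inputs from the paragraph after Table 3: first antenatal visit at 25 weeks' gestation on average, and recommended PCR testing five months later on average. The article gives no gestational age at birth. I assume 40 weeks and show 37 to 41.

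Reproducing the lag: months = (weeks at birth − 25 + infant age in weeks) / 4.348. With birth at 40 weeks:

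- test at 6 weeks: (40 − 25 + 6) / 4.348 = 4.8 months
- test at 8 weeks: (40 − 25 + 8) / 4.348 = 5.3 months
- test at two months: (40 − 25 + 8.7) / 4.348 = 5.45 months

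All three round to the stated five months.

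The other way round: infant age at five months = 25 + 5 × 4.348 − weeks at birth = 46.7 − weeks at birth.

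| Birth (weeks) | Infant age at five months (weeks) |
|---|---|
| 41 | 5.7 |
| 40 | 6.7 |
| 39 | 7.7 |
| 38 | 8.7 |
| 37 | 9.7 |

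For birth at 40 weeks or earlier, the plan's average recommended test time lies past the Table 3 limit. Only birth at 41 weeks puts it just inside. The lag therefore fits testing at about six to eight weeks better than a numerator closed before six weeks.

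**3. Reach of a literal reading**

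Under Trial design, each country has six intervention and six comparison facilities, so Côte d'Ivoire has 12 of 36. Suppose a share f of tests falls under the age limit, similar in both arms and in both periods. Each facility's measured proportion is then f times the true one, and so is the measured difference in change. Any f below 1 dilutes the effect, and an f that varies by country makes the countries non-comparable. The article gives no ages at test, so f cannot be estimated.

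**The case against.** The strongest reply is that this is a drafting slip with a recoverable meaning. The text, Table 1 and the five-month lag all point to about six to eight weeks, which leaves the sign in Table 3 as the outlier. The section on adapting the tool says that standard operating procedures were written for data collection. They are not shown and may hold the correct rule. This stands in part: nothing proves that any test has been left out. It does not remove the conflict. Reading the limit as six weeks or less would still exclude the two-month test in Côte d'Ivoire and would still differ from the abstract.

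The abstract is also weaker evidence than the other two places. A diagnosis may follow the test, so part of the gap between six and eight weeks may reflect a different event. That is fair, but which event is counted then needs settling too.

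A reader might go further and put a number on the loss: if Côte d'Ivoire contributed nothing, a 20-point gain would shrink to 20 × 24/36 = 13.3 points, close to the 10.6-point detectable difference. The documents do not support this. Under Sample size, both the 20 points and the 10.6 points were set for the antiretroviral outcome, and no effect or standard deviation is given for infant testing. Moreover, 13.3 still exceeds 10.6.

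A reader might also infer that the five-month look-back in the denominator must change. It need not: 4.8 and 5.45 months both round to five.

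**Conclusion.** The inconsistency is certain, because it rests on the wording alone. One primary outcome has three timings and at least two counted events, and nothing in the article reconciles them.

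The consequence is conditional. If Table 3 is followed literally, tests done on the schedule that the text describes are not counted, most clearly in the 12 Côte d'Ivoire facilities. That would dilute any effect, assuming the share of tests under the limit is similar across arms and periods, and it would make the countries non-comparable. How large the loss would be is unknown.

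A reader might conclude that such tests are in fact being lost. The article does not show this, since it does not say which definition the extractors use. The conflict with the five-month lag depends on the assumed birth at 40 weeks or earlier. The conflict between the text and Table 3 needs no such assumption.

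**What to change.** Give the abstract, the text and Table 3 the same definition:

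- one counted event, either the test or the diagnosis;
- one age window for counting, country-specific where needed and identical in both arms, that includes the scheduled test visit the text describes.

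Replace the under-six-weeks limit in Table 3 accordingly. A grace period is optional. The denominator look-back can stay as it is. This settles which tests are counted. It takes no position on when infants should be tested, and the passages that differ on that must be reconciled by the investigators.

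The cost is a change of wording in the abstract, text, Table 3 and, where it carries the same limit, the extraction form. Any months already extracted under a different rule need re-extraction from the same facility registers.

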### Côte d’Ivoire

Study facilities are located in three northern regions of Côte d’Ivoire (Gbêké, Hambôl, Poro-Tchologo-Bagoue) which had an estimated adult HIV prevalence of 4.4%, 4.4%, and 2.5% respectively in 2011 – 2012 [45]. PMTCT services in Côte d’Ivoire are provided primarily through public sector health facilities, as well as some private facilities. In 2011, 734 health facilities actively provided PMTCT services in Côte d’Ivoire, of which 113 are located in the study regions. The World Health Organization’s PMTCT Option B regimen was adopted as national policy in November 2012.

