### Analysis

The primary analysis approach to assess the impact of the SAIA intervention will rely on paired t-tests comparing the average outcome measures over the 12 months preceding the intervention, compared with the average over the three months directly following the intervention period, for the three study outcomes. As a secondary analysis approach, segmented regression analysis that controls for baseline outcome levels and trend to compare the monthly averages before versus after the intervention will be carried out for all three study outcomes. Change points will include a node at the beginning of the intervention period to reflect the introduction of the intervention; two additional terms will be added to the model at the end of the six-month intervention period to indicate the level change and trend change post intervention. To account for a three-month lag in the impact of the intervention, data from the first three months post initiation of the intervention will be excluded from analysis. Sub-analyses will be carried stratified by country and facility size to assess subgroup effects.

Because facilities will be randomly selected and allocated to intervention and control facilities, we do not expect to perform adjusted analyses. However, descriptive characteristics will be compared between intervention and comparison facilities using student’s *t*-test and chi-square tests to assess potential imbalance between study arms, and subsequent analyses will consider covariates significant in bivariate analysis for inclusion in the final model in a stepwise fashion. In addition, because outcomes are reported as a monthly summary measure at the facility level, no additional procedures will be implemented to control for potential intra-class correlation at the cluster (health facility) level. Autocorrelation will be assessed using the Durbin-Watson statistic, and adjusted for if appropriate.

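### ARV use and infant PCR testing are lagged monthly ratios that can exceed 100%; averaging them month by month adds noise and inflates gains if monthly HIV-positive counts are small

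*Protocol article*

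**What the plan says.** The protocol article (Study measures, Primary study outcomes) puts all three outcomes on one scale: "All primary outcome measures are calculated as a monthly average (continuous percentage between 0% and 100" (per cent). It then says that measures 2 and 3 "include numerators and denominators from different time periods due to time progression between service contacts".

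- **Measure 1 (Table 3):** women tested at first ANC visit over first ANC visits, same month, no lag.
- **Measure 2:** women starting AZT prophylaxis or cART this month, over women testing positive in ANC three months earlier. The text below the table gives the delay differently: it "is estimated to be two months", and the next sentence justifies it by a mean gestational age at first visit, "or approximately three months before initiation of AZT or cART".
- **Measure 3:** infant PCR tests this month, over women testing positive in ANC five months earlier. The reason given is also an average: "The recommended timeframe for PCR testing of infants is on average five months after the first ANC visit".

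The Analysis section describes the primary test as "comparing the average outcome measures over the 12 months preceding the intervention" with the average over the three months after it. It mentions neither weighting nor pooling of counts. The Sample size section plans on measure 2, with baseline 50%, a 20-point gain and an SD of yearly change scores of 11 points.

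**The concern.** A percentage is confined to 0% to 100% when everyone in the numerator is also in the denominator. For measures 2 and 3 that would need every woman to follow the stated lag exactly, yet the lags are given only as means. Suppose two women test positive in May and three in June. If both May women and one early June woman start treatment in August, the August value is 3/2 = 150%. If nobody tested positive in May, August has no value.

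A simple average of such values gives a month with one positive woman the same weight as a month with ten. It also gives large ratios to months whose denominator happens to be small. Two of the three primary outcomes are affected, including the one that sets the sample size. At stake are the precision of the primary comparison and the size of the reported gain.

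**Working it through.** **1. The plan's own figure.** A two-sample t-test on facility change scores (SD 11, two-sided α 0.05, power 0.80, noncentral t) gives detectable differences of 19.75, 13.16 and 10.57 points for 6:6, 12:12 and 18:18. Table 4 states 19.7, 13.2 and 10.6, so it reproduces. Any sampling noise in the monthly ratios has to fit inside that SD of 11.

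**2. How many women per month?** The article gives no counts. Let m be the mean number of HIV-positive ANC tests per facility-month, taken as first visits × adult prevalence (assumed to apply to ANC clients, with all of them tested).

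| Assumed first visits per month | Côte d'Ivoire (2.5–4.4%) | Kenya (4.3–4.9%) | Sofala (15.5%) |
|---|---|---|---|
| 100 | 2.5–4.4 | 4.3–4.9 | 15.5 |
| 400 | 10–17.6 | 17.2–19.6 | 62 |

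**3. Zero denominators.** With Poisson counts, P(D = 0) = e^−m, which is 5.0% at m = 3, 0.7% at m = 5 and practically nil at m = 10. The chance of at least one such month in twelve is 1 − (1 − e^−m)^12, which is 46% at m = 3 and 8% at m = 5.

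**4. Bias of the monthly ratio.** Assumptions: the same women are followed, 25%, 50% and 25% of those treated start at 2, 3 and 4 months, the denominator is shifted by three months, and true coverage is p. Half of the numerator then comes from the denominator's own cohort and half from neighbouring months. So, approximately:

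E(ratio) = p × [0.5 + 0.5 × m·E(1/D | D > 0)]

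The factor m·E(1/D | D > 0) is 1.29, 1.13 and 1.056 at m = 5, 10 and 20. At p = 0.50 this gives:

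- m = 5: 0.50 × (0.5 + 0.645) = 57.3%
- m = 10: 0.50 × (0.5 + 0.565) = 53.3%
- m = 20: 0.50 × (0.5 + 0.528) = 51.4%

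A true 20-point gain is multiplied by the same bracket: 22.9, 21.3 and 20.6 points.

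**5. Simulation of the same model** (200,000 facilities per setting, 12 months before and 3 after, months with D = 0 dropped):

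| | m = 5 | m = 10 | m = 20 |
|---|---|---|---|
| Baseline level, monthly mean v pooled (true 50%) | 57% v 50% | 53% v 50% | 51% v 50% |
| Months above 100%, coverage 50% / 70% | 8% / 18% | 3.5% / 13% | 0.7% / 7% |
| Sampling SD of change, monthly mean v pooled (points) | 26.1 v 17.3 | 14.8 v 11.9 | 8.9 v 8.3 |
| Mean change, no true change, monthly mean v pooled | 0.0 v +0.6 | 0.0 v +0.3 | 0.0 v +0.1 |
| True 20-point gain if months were capped at 100% | 16 | 18 | 19 |

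**6. What this means for Table 4.** The detectable difference scales with the SD. If sampling noise were the only source of variation, 18:18 would detect 10.57 × 26.1/11 = 25.1 points at m = 5 (pooled: 10.57 × 17.3/11 = 16.6). At m = 10 it would detect 10.57 × 14.8/11 = 14.2 (pooled: 10.57 × 11.9/11 = 11.4). At m = 20 the noise fits inside the planned SD under either method.

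**The case against.** **Scope.** A reader might infer that all three primary outcomes are at fault. They are not: measure 1 counts the same women in the same month and cannot exceed 100%.

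**Counts.** That few women test positive each month is an assumption. The 12 highest-volume eligible facilities were chosen in each country, and Sofala's 15.5% prevalence gives about 15 women a month even at 100 visits. This stands. Low counts are plausible mainly in Côte d'Ivoire, "which had an estimated adult HIV prevalence of 4.4%, 4.4%, and 2.5% respectively", and in Kenya.

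**The planned SD.** If the 11 points came from this same measure, very small counts are unlikely to be typical. Under the model above, a 12-v-12-month change has a sampling SD of √2 × 11.1 = 15.7 points at m = 5 and √2 × 6.2 = 8.8 at m = 10. The article does not say which measure the SD came from, so this limits the likely size without settling it.

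**Overlap.** The lag is meant to line up the same cohort, so calling the groups wholly different women would be too strong. A model with no overlap at all gives 65% at m = 5, but that is an upper bound and is not used here.

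**False effect.** Bias in the level might suggest a spurious intervention effect. It nearly cancels before versus after when nothing changes. A 20% rise in women tested, with coverage unchanged, moved the measured change by only about −2 to +1 points even with no overlap.

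**Truncation and zero months.** The article does not say that values are capped; the range may only describe a scale. Handling of zero months and weighting may be set out in the full protocol or SAP. What remains is an outcome definition that contradicts its stated range.

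**Infant denominator.** Adding women already known to be HIV-positive would redefine the outcome and may need extra extraction. It is a separate question.

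**Conclusion.** The point holds for measures 2 and 3 only. Their stated 0% to 100% range conflicts with their Table 3 definition, and the ARV lag is given as both two and three months. Neither conclusion needs an assumption.

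The size does depend on assumptions: Poisson counts, lags spread over 2 to 4 months, true coverage 50%, and unweighted averaging, which is the natural reading but is not stated. At 5 HIV-positive women per facility-month the effect is substantial (level inflated by 7 points, change SD 26 against 17 when pooled). At 10 it is moderate (3 points; 14 to 15 against 12). At 20 it is slight (1 point; 9 against 8). A true 20-point gain would read as about 23, 21 and 20.5 points.

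The harm is to precision and effect size. The documents do not support reading it as a source of false positive results, or as evidence that the facilities do have few HIV-positive women. The change is worth making because it is cheap.

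**What to change.** For measures 2 and 3:

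1. In the primary analysis, compute each facility's period value as total numerator over total lag-shifted denominator, once for the 12-month baseline and once for the 3-month post period. Keep monthly values for plots and for the segmented regression.
2. Remove the 0% to 100% limit for these two measures and state that values above 100% are not truncated.
3. Reconcile the ARV lag between Table 3 (three months) and the text below it (two months, then about three), and apply one lag throughout.

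Measure 1 needs no change to its range.

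**Cost.** This changes analysis wording and uses the monthly counts already being extracted from the registries. High-volume months will weigh more within a facility. Pooling over windows of 12 and 3 months leaves a small ratio bias at low counts, about 0.4 to 3 points at 5 women per month depending on the lag spread. It should be similar in both arms and so drop out of a between-arm comparison of changes, which is the contrast that Table 4 is built on. It would not drop out of a before-after comparison within one arm.
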